## Recording and reporting of Adverse Events and protocol violations

### Adverse event recording

Grade 3 and 4 adverse events will be
**recorded** in the case report form and entered to the study database. Grade 1 & 2 events will not be recorded since in a severe disease such as cryptococcal meningitis the number of low grade adverse events is likely to be high representing a large reporting burden which may impact upon the quality of recording and reporting of more important grade 3 and 4 adverse events.

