## Other effects

An early trial of high dose Tamoxifen (equivalent to >450mg/day) in patients with epithelial tumours reported a sense of light-headedness and unsteady gait in a proportion of patients, which resolved within 2–5 days of stopping the drug
^26^. Tamoxifen does not have any expected haematological or hepatic side effects.

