### Secondary aims

The secondary aims are to

-demonstrate the proof of concept that Tamoxifen can be safely administered with amphotericin and fluconazole to generate preliminary data that will support a larger phase 3 trial of Tamoxifen in cryptococcal disease-determine the effects on survival and disability at 10 weeks following study treatment initiation,-define the pharmacokinetics of amphotericin, fluconazole and Tamoxifen in blood and CSF-better understand the pathogenesis of cryptococcal meningitis through defining the species, subtype, drug susceptibility and in situ gene expression of the infecting
*Cryptococcus* and host response

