***Visual deficit at 10 weeks.*** Visual deficit occurs in 5–40% of patients with cryptococcal meningitis depending upon underlying immune status
^5,
8^. The pathogenesis is unclear. We will compare the incidence of blindness and other visual deficit between treatment groups. Visual deficit will be assessed using a simple 6 point scale, as used in previous studies (see
Table 3).

***Time to new neurological event or death until 10 weeks.*** A neurological event is defined as a fall in Glasgow coma score by ≥2 points for ≥2 days from the highest previously recorded Glasgow coma score (including baseline) or the occurrence of any of the following adverse events: cerebellar symptoms, coma, hemiplegia, paraplegia, seizures, cerebral herniation, new onset blindness or deafness, or cranial nerve palsy.

***Longitudinal measurements of intracranial pressure during the first 2 weeks.*** Intracranial pressure (ICP) will be measured at study entry, day 3, 7, and 14, and if clinically indicated (depending on local practice). The main outcomes are longitudinal ICP-measurements until day 14.

Clinical need and local practice will determine the frequency of lumbar punctures post day 14 and clinician’s diagnoses of raised ICP based upon the presence of headache, nausea, diurnal and postural variation, relief with lumbar puncture and presence of papilloedema. Thus, these measures will only be descriptively analyzed.

***CD4 count at 10 weeks.*** CD4 count measurement is indicated in HIV infected patients, and CD4 lymphopenia has been described in HIV uninfected patients with cryptococcal meningitis. Moreover, Tamoxifen may reduce CD4 cell apoptosis which may be beneficial
^47^.

***Blood and CSF concentrations of amphotericin, Tamoxifen and fluconazole.*** Pharmacological data on antifungal drugs are lacking. Dosing has been inferred from studies in healthy volunteers, or patients with other diseases. There are no studies of combination therapy at the doses currently recommended
^48–

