### Intervention arm: Induction phase treatment (days 1–14)

Tamoxifen will be given orally in a dose of 300mg/day for the first 14 days following randomization. It will be administered by nasogastric tube where patients are unconscious. In addition patients will receive amphotericin 1mg/kg once daily i.v. and fluconazole 800mg once daily orally. The Tamoxifen will be administered in the morning combined with amphotericin and fluconazole dose.

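### The neurological-event endpoint counts listed adverse events with no grade limit, while the recording rule leaves out grade 1 and 2 adverse events

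*Protocol article*

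**What the plan says.** Three parts of the protocol bear on whether a neurological event is captured.

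- **Secondary endpoints, time to new neurological event or death until 10 weeks.** An event is either a sustained fall in Glasgow coma score or "the occurrence of any of the following adverse events: cerebellar symptoms, coma, hemiplegia, paraplegia, seizures", with further items that include cranial nerve palsy. No grade is stated. The analysis section treats this endpoint like overall survival and adds no grade.
- **Adverse event recording.** The section opens "Grade 3 and 4 adverse events will be" recorded and entered in the database, and continues: "Grade 1 & 2 events will not be recorded since in a severe disease such as cryptococcal meningitis" their number is likely to be high and could harm the recording of more important events.
- **Clinical monitoring.** Patients are watched for new neurological events, defined as new focal signs or a fall in coma score, with a condition of more than 7 days of prior stability or improvement. No grade is stated, and cerebellar symptoms are not named.

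Two other statements give context. A secondary aim is to "demonstrate the proof of concept that Tamoxifen can be safely administered with amphotericin and fluconazole". Under Other effects, an early high-dose trial is said to have "reported a sense of light-headedness and unsteady gait in a proportion of patients, which resolved within 2–5 days of stopping the drug".

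**The concern.** An endpoint built on adverse events can be no more complete than the adverse-event record. If the record stops at grade 3, events on the endpoint's list that were graded 1 or 2 may never reach the analysis, although the endpoint definition includes them. The protocol does not say which rule prevails. One site could record a mild cerebellar sign because it is on the endpoint's list, and another could omit it because it is grade 2.

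Treatment is open-label, so that choice could also differ by arm. The comparison would then partly reflect recording practice.

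The ambiguity may also touch the intervention. Unsteady gait, the high-dose effect mentioned under Other effects, can reasonably be read as a cerebellar symptom. Whether it enters the endpoint, and whether it appears in any safety summary, would depend on which rule staff followed.

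**Working it through.** No stated sample size, power or event figure is in question, so the check compares the text.

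**Step 1. Does the endpoint intend a grade limit?** None is written. The adverse-event endpoint, in the same list of secondary endpoints, is explicitly limited to grade 3 or 4 and serious events. The general definition of an adverse event carries no grade. The natural reading is that listed neurological events count at any grade, although the protocol does not say so outright.

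**Step 2. Follow a grade 2 cerebellar symptom through the protocol.**

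| Section | Outcome |
|---|---|
| Endpoint definition | Qualifies |
| Adverse event recording | Not recorded |
| Clinical monitoring | Captured only if it is judged a new focal sign and the stability condition is met |
| Adverse-event analysis and monitoring-board report | Serious and grade 3–4 events are specified; no stated route for this event unless serious |

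**Step 3. Does Clinical monitoring close the gap?** Only partly. A cranial nerve palsy is a focal sign, so that route could catch it. Cerebellar symptoms are not named. The wording does not settle whether the condition of more than 7 days' stability governs both limbs or only the coma-score limb. If it governs both, nothing on days 1 to 7 can qualify, which is 7 of the 14 days of tamoxifen. The endpoint definition has no such condition.

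**Step 4. Could grade matter for the effect described?** Other effects gives no grade and no rate. Grading follows CTCAE, with a generic scale for events that CTCAE does not describe. On the generic scale, grade 3 requires an event that is disabling, limits self-care, or indicates hospitalisation or its prolongation. On that scale, unsteady gait can fall below grade 3; the protocol does not show that it usually does.

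**Step 5. Illustration only.** Let p be the any-grade incidence in the tamoxifen arm and s the share of cases at grade 3 or above. Both are assumptions. With 25 patients per arm (Sample size and power considerations), recording grade 3 and above only:

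- expected recorded cases = 25 × p × s
- P(at least one recorded) = 1 − (1 − p·s)^25

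The column s = 1.00 is equivalent to recording every grade.

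| p | s = 0.10 | s = 0.25 | s = 0.50 | s = 1.00 |
|---|---|---|---|---|
| 0.10 | 0.22 | 0.47 | 0.72 | 0.93 |
| 0.20 | 0.40 | 0.72 | 0.93 | 0.996 |
| 0.40 | 0.64 | 0.93 | 0.996 | >0.99 |

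For p = 0.10 and s = 0.10, for example, 1 − 0.99^25 = 0.22, with 0.25 expected recorded cases out of 2.5. For p = 0.40 and s = 0.50, 1 − 0.80^25 = 0.996, with 5 out of 10. The loss ranges from large to negligible and depends heavily on s, which the protocol does not give.

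**The case against.** The strongest reply is that the grade 3–4 threshold is a deliberate choice with a stated reason, and that it agrees with the adverse-event endpoint and its analysis. That stands: the threshold is not an error for general adverse events, and this point does not ask for its removal.

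It can also be said that most items on the endpoint's list (coma, hemiplegia, paraplegia, seizures, herniation, new blindness) are unlikely to be low grade. Staff also assess inpatients daily, and any event of concern may be reported as an unexpected serious event. This limits the exposed part mainly to cerebellar symptoms and milder cranial nerve palsies. It does not remove it, because the monitoring definition is different and reporting an event of concern is discretionary.

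A reader might infer that the recording rule hides most of the neurotoxicity of this regimen. The documents do not support that. The report comes from "An early trial of high dose Tamoxifen (equivalent to >450mg/day) in patients with epithelial tumours", whereas here "Tamoxifen will be given orally in a dose of 300mg/day for the first 14 days following randomization", and no grade or frequency is given. A tenfold loss of cases would only restate an assumed 10% share at grade 3.

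A reader might also infer that a reversible drug effect would be wrongly booked as a disease event. That does not follow either. The endpoint has no causality condition, and neurological harm from the drug properly counts in a randomised comparison.

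**Conclusion.** The inconsistency holds in a limited form. The endpoint counts listed adverse events without a grade, the recording rule excludes grades 1 and 2, and the monitoring definition only partly bridges them. Qualifying lower-grade events can be dropped, or their capture left to site practice in an open-label trial.

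It affects one secondary endpoint and the scope of the safety conclusion; the primary endpoint, early fungicidal activity, is untouched. The conclusion rests on reading the absence of a grade as meaning any grade, which the contrast with the adverse-event endpoint supports.

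Its numerical size is unknown. The detection probabilities are illustrative, and they do not allow for dizziness or gait disturbance caused by the meningitis itself.

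**What to change.** Keep the grade 3–4 rule for general adverse events. Add to Adverse event recording that every event listed in the neurological-event endpoint, including unsteady gait or other cerebellar signs, is recorded at any grade with onset and resolution dates, identically in both arms. State that these events count towards the endpoint regardless of grade or suspected cause. Do not sort endpoint events by their timing from the last tamoxifen dose, because controls receive none. Align the definition in Clinical monitoring with the endpoint, including the status of the 7-day stability condition.

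The cost is a small extra recording burden for a handful of items.

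Trial status says that enrolment has finished and analysis is under way. For this trial, therefore, the endpoint rule should be stated before the endpoint is analysed. Where lower-grade events were not recorded, the safety conclusion should say that it covers grade 3–4 and serious events only. The recording exception can be carried into any larger trial.

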### Adverse event reporting

Serious adverse events and serious unexpected adverse events will be
**reported** to the Principal Investigator within 3 days of occurrence, or sooner according to local requirements. The Principal Investigator will report all unexpected serious adverse events to the DSMB within 10 days of occurrence. Unexpected serious adverse events will be reported to the responsible ethical committees within 10 days of occurrence or as required by the committee. Serious adverse events will be reported to the local IRBs on a monthly basis.

### Protocol violations

Protocol violations are events which contradict or omit protocol instructions. Violations which compromise patient safety or the integrity of trial data will be recorded and reported to the responsible Ethics Committees as required by the regulations of each Committee.

## Statistics

### Sample size and power considerations

Sample size considerations were based on simulation using data from two previously published trials in cryptococcal meningitis conducted in Vietnam
^8,
9^: 96 patients from the BK trial (all recruited at HTD) with at least one quantitative fungal count measurement randomized to amphotericin B plus fluconazole, and 97 randomized to amphotericin B plus flucytosine; plus 49 patients from the CryptoDex trial recruited at HTD or Cho Ray Hospital randomized to placebo (all of these received antifungal treatment with amphotericin B plus fluconazole).

The first set of simulations assumed that the Tamoxifen group was associated with a similar effect on Early Fungicidal Activity (EFA) as amphotericin B plus flucytosine. For sample sizes ranging from 15-30 patients per group, we repeatedly sampled patients from both included BK study arms of that size with replacement, analyzed them, i.e. compared EFA between the two groups, and then determined the proportion of significant results (i.e. the estimated power).

For the second set of simulations, the control group consisted of the combined 145 patients from the BK study and 04CN receiving amphotericin B plus fluconazole. For assumed EFA treatment effects ranging from -0.16 to -0.10 log
_10_CFU/ml per day faster declines in the intervention group, we generated hypothetical intervention group data by simulating this treatment effect on top of the observed fungal count measurements for patients receiving amphotericin B plus fluconazole. Power was then determined based on resampling-based simulation as for the first set of simulations.

Estimated power was based on 10 000 repetitions of each simulation experiment. Estimating EFA based on a mixed model accounting for the detection limit of fungal count measurements was not feasible because this would require excessive computing time. Thus, we used a simple mixed model ignoring the detection limit for the simulations instead but removed values after the first undetectable (zero) fungal count measurements and kept the first fungal count of zero only if it lead to a steeper estimated least-squares decline for that patient compared to omitting the measurement.

Results for both sets of simulations are shown in
Figure 3. Based on the first simulation study, n=25 subjects per group provide approximately 80% power to detect a difference in EFA of similar size as the difference between amphotericin B plus fluconazole and amphotericin B plus flucytosine observed in the BK study. Based on the second simulation study, n=25 subjects per group provide 80% and 90% power to detect a difference in EFA of -0.11 or -0.13 log10CFU/ml/day, respectively. We consider that this size of effect is likely to deliver a clinical benefit. All simulations were performed using
R software version 3.2.2
^59^.

**Figure 3. f3:**
[figure not shown]
Screening study flow diagram.

*Analysis*

## Analysis of the primary endpoint: early fungicidal activity (EFA)

All recorded longitudinal quantitative fungal count measurements up to day 17 (allowing for some delays in the day 14 measurements) will be included in the analysis. EFA will be modeled based on a linear mixed effects model with longtitudinal log
_10_-CSF quantitative culture fungal counts as the outcome, interaction terms between the treatment groups and the time since enrolment of the measurement as fixed covariates and random patient-specific intercepts and slopes. The lowest measurable quantitative count is 5 CFU/ml and values below the detection limit (which correspond to recorded values of 0) will be treated as <4.5 CFU/ml, i.e. non-detectable measurements will be treated as left-censored longitudinal observations in the analysis as we have done previously
^8^.

Based on this model, EFA will be compared between the two treatment arms in all patients (intention to treat), in the per-protocol population, and subgroups defined by HIV status (uninfected; infected) and baseline fungal burden (<5 log
_10_ CFU/ml; ≥5 log
_10_ CFU/ml).

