## Background

Worldwide cryptococcal meningitis results in approximately 625 000 deaths each year, most occurring within 3 months of diagnosis
^1^. It is the leading cause of death in HIV patients in Asia and Africa affecting 3.2% of the HIV infected population per year
^1^. Despite improvements in access to HIV care, the WHO estimates that even if 80% access to HIV treatment is achieved, there will be 6.5 million AIDS deaths p.a. by 2030
^2^. Thus, CM is likely to remain a significant health burden for the foreseeable future. While cryptococcal meningitis predominantly occurs in HIV infected patients, patients with other forms of immunosuppression are also affected
^3,
4^. Furthermore, in Viet Nam we see disease in apparently immunocompetent patients (N = 30 each year at the Hospital for Tropical Diseases and Cho Ray Hospital) due to infection with
*Cryptococcus neoformans* var.
*grubii*, or, more rarely,
*C. gattii*
^5^.

There has been no major advance in the treatment of cryptococcal meningitis since the 1980’s, and the 90 day case fatality rate of cryptococcal meningitis remains unacceptably high, estimated at 55% in Asia and 70% in Africa
^1^. The mainstays of induction therapy are drugs that are over 50 years old – amphotericin B and flucytosine - although these are often poorly available where disease burden is highest
^6,
7^. While amphotericin monotherapy is undoubtedly superior to fluconazole monotherapy, amphotericin combination therapy has only recently been shown to reduce mortality when compared with amphotericin monotherapy in a randomized controlled trial in Vietnam
^8^. In this study, in Vietnamese patients receiving gold standard treatment with amphotericin and flucytosine, the death rate at 10 weeks and 6 months was 31% and 35%. This compared with 33% and 46% in patients receiving amphotericin-fluconazole induction therapy (the current WHO guideline), and was significantly better than in patients receiving prolonged amphotericin monotherapy, where the death rates were 44% and 54% respectively
^8^. A biological explanation for these better outcomes is that the amphotericin-flucytosine combination has increased sterilising power – it results in significantly more rapid clearance of yeast from cerebrospinal fluid than amphotericin monotherapy

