### Randomization

Randomization will be 1:1 to either Tamoxifen augmented or standard antifungal therapy. Block randomization with stratification by hospital of enrolment and by HIV infection status, and variable block sizes of 4 and 6, respectively, will be used to assign subjects to treatment. The randomization list will be generated according to OUCRU standard operating procedures. In brief, the Research Biostatistician will set up statistical code to generate the randomization list and transfer it to the central Study Pharmacist. The Study Pharmacist will change the random seed, i.e. the initialization of the random numbers generator, in the statistical code in order to blind the Research Biostatistician and then run the code to prepare the final randomization list for treatment preparation. The randomization list will be password protected and stored on a secure server to which only the Study Pharmacist has access.

Based on the randomization list, the central Study Pharmacist will generate identical sealed treatment packs for each study ID and distribute them to the sites in batches as required. All treatment packs will be identical in appearance and will contain either Tamoxifen and fluconazole or fluconazole alone. Each pack will contain sufficient fluconazole for the first 2 weeks of treatment. Enrolment logs specific to each ward will be used to assign patients to the next available sequential number and corresponding sealed treatment pack.

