## Analysis of secondary endpoints

### Survival until 10 weeks after randomization

Overall survival will be visualized using Kaplan-Meier curves and modeled using the Cox proportional hazards regression model with stratification by HIV status. In addition, survival will be modeled with a multivariable Cox regression model including the following covariates in addition to the treatment group: baseline log
_10_-fungal load, Glasgow coma score less than 15 (yes or no), HIV infection status, and ARV treatment status at study entry (naïve or experienced).

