### Disability at 10 weeks.

The disability score at week 10 follow-up is defined as the higher (worse) of “ the two simple questions” and the Rankin score assessed at that time point, and will be categorized as good outcome, intermediate disability, severe disability, or death (in case the patient died before 10 weeks) as previously described
^45^. The ordinal 10-week score (“good”>”intermediate”>”severe”>”death”) will be compared between the two arms with a proportional odds logistic regression model depending on the treatment arm and HIV infection status. The result will be summarized as a cumulative odds ratio with corresponding 95% confidence interval and p‐value. Patients lost to follow up will be analyzed according to their last recorded disability status. If the rate of patients lost to follow-up exceeds 10%, we will also perform an alternative analysis based on multiple imputation of missing values.

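### The primary EFA model omits HIV status and hospital, the factors that stratify randomisation; if HIV status predicts clearance rate, some power is given away

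*Protocol article*

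**What the plan says.** The Randomization section specifies "Block randomization with stratification by hospital of enrolment and by HIV infection status", with 1:1 allocation.

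The section on analysis of the primary endpoint describes a linear mixed model for log10 CSF fungal counts, left-censored at the detection limit. Its terms are given as "interaction terms between the treatment groups and the time since enrolment of the measurement as fixed covariates and random patient-specific intercepts and slopes". Neither HIV status nor hospital is listed. For EFA, HIV status appears only in comparisons within "subgroups defined by HIV status (uninfected; infected) and baseline fungal burden".

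Most secondary analyses use HIV status:
- Survival is "modeled using the Cox proportional hazards regression model with stratification by HIV status", and time to neurological event or death is handled in the same way.
- Disability uses a "proportional odds logistic regression model depending on the treatment arm and HIV infection status".
- Both QTc analyses, visual acuity and CD4 change adjust for HIV status. IRIS and relapse are stratified by it.

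Two do not. Intracranial pressure follows the primary mixed model, and adverse events use Fisher's exact test. Hospital is in no stated model.

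**The concern.** Stratified randomisation balances a factor across arms, so the factor contributes little to the chance variation of the treatment contrast. If the factor predicts slope and is left out of the model, its variance is still counted as random-slope variance. The reported standard error then exceeds the true sampling variation. The test is conservative and power is lost that the design had already secured.

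The endpoint that decides whether a larger trial follows would thus use less of the design than survival or disability does. The trial enrols HIV-infected and uninfected patients together, and the protocol itself treats HIV status as worth a stratum and an EFA subgroup. With 25 patients per arm, a few points of power are worth having if they cost almost nothing.

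**Working it through.** **Inputs from the protocol.** "n=25 subjects per group provide 80% and 90% power to detect a difference in EFA of -0.11 or -0.13 log10CFU/ml/day, respectively". Allocation is 1:1 with blocks of 4 and 6.

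**Assumptions.**
- The test is two-sided at 5% (level and sidedness are not stated).
- The HIV-uninfected share p is 20% to 35%. The Background reports apparently immunocompetent cases as "N = 30 each year at the Hospital for Tropical Diseases and Cho Ray Hospital", and recruitment ran from November 2017 to May 2018, about 7 months. Enrolling all of them would give 30 × 7/12 = 17.5 of 50, or 35%. The 20% is a lower value chosen for range.
- The difference d in mean EFA slope between HIV groups is 0 to 0.15 log10 CFU/ml/day. The protocol gives no value.

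**Step 1: the stated power.** It came from resampling earlier trial data and no SD is printed, so it cannot be reproduced directly. It can be checked for internal consistency.
- 80% at 0.11: SE = 0.11/(1.960 + 0.842) = 0.0393. Slope SD = 0.0393 × √(25/2) = 0.139, variance 0.0193.
- 90% at 0.13: SE = 0.13/(1.960 + 1.282) = 0.0401, SD 0.142.
- With SD 0.139, power at 0.13 is 91.2% against the stated 90%. The two figures agree.

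**Step 2: formula.** Take 0.139 as the within-stratum SD. Omitting HIV status adds p(1−p)d² to the modelled slope variance, so the SE ratio is r = √(1 + p(1−p)d²/0.0193). Because the true sampling variation is unchanged, power ≈ Φ(2.80 − 1.96r) and type I error ≈ 2(1 − Φ(1.96r)).

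| p | d | r | Type I error | Power at 0.11 |
|---|---|---|---|---|
| any | 0 | 1.00 | 5.0% | 80.0% |
| 20% | 0.05 | 1.01 | 4.8% | 79.4% |
| 20% | 0.10 | 1.04 | 4.1% | 77.7% |
| 20% | 0.15 | 1.09 | 3.3% | 74.7% |
| 35% | 0.05 | 1.01 | 4.7% | 79.2% |
| 35% | 0.10 | 1.06 | 3.8% | 76.7% |
| 35% | 0.15 | 1.13 | 2.8% | 72.5% |

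**Step 3: simulation.** Per-patient slopes were simulated for 50 patients with stratified blocks of 4 and 6, 5,000 runs per scenario. Hospital was given no effect. A t-test was compared with a linear model adjusting for HIV status and hospital.

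| p | d | Unadjusted power | Adjusted power | Unadjusted type I error |
|---|---|---|---|---|
| 20% | 0 | 78.3% | 78.0% | 4.8% |
| 20% | 0.05 | 78.3% | 78.6% | 4.3% |
| 20% | 0.10 | 76.6% | 78.8% | 4.0% |
| 20% | 0.15 | 72.3% | 78.1% | 3.5% |
| 35% | 0 | 77.9% | 77.7% | 4.6% |
| 35% | 0.05 | 78.0% | 78.4% | 5.0% |
| 35% | 0.10 | 74.7% | 78.1% | 4.0% |
| 35% | 0.15 | 71.2% | 79.6% | 2.9% |

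The gap is under 1 point at 0.05, 2.2 to 3.4 at 0.10 and 5.8 to 8.4 at 0.15. At d = 0 adjustment changes power by 0.3 points or less, within simulation error. At p = 35% and d = 0.15 the mean unadjusted SE is 0.0441 against a true sampling SD of 0.039 to 0.040.

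**Limit of the check.** It uses one slope per patient, not the left-censored mixed model. Full mixed-model fits were tried, did not converge reliably and were discarded.

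**The case against.** The strongest reply is that this is an efficiency preference and not an error. The estimate is unbiased, type I error is not inflated, and a simple conservative primary model is a legitimate choice. That stands.

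The assumed slope differences can also be called generous. A shift of 0.10 to 0.15 is about as large as the treatment effect the trial targets (0.11), and nothing in the protocol says HIV status moves EFA that far. That stands too, and it is why 0 and 0.05 are tabulated.

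A reader might infer that the SE is in fact too wide and that power has been lost. The documents do not support this without a slope difference by HIV status or hospital, and they report none. A reader might also infer that the stated 80% and 90% are overstated. They were simulated with a simple mixed model for which no stratification covariates are mentioned, so they do not presuppose adjustment. A shortfall would arise only if HIV-uninfected patients add slope variance that the source data lacked. One source trial was in HIV-associated disease; the protocol does not state the HIV mix of the other.

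The contrast with the secondary analyses supports adding HIV status but not hospital, which no stated model uses and for which no loss has been calculated.

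On the subgroups, the protocol says only that arms will be compared within them. A reader might infer that one significant and one non-significant subgroup would be read as effect modification, but no such rule is stated. The risk of that reading is real: with an identical true effect of 0.11 and an assumed 17 and 8 patients per arm, power is 64% and 35%, so the chance that exactly one is significant is 0.637 × 0.646 + 0.363 × 0.354 = 54%. It remains a secondary point.

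The omission cannot be put down to detail left for an analysis plan. The protocol lists the model's terms, and it names HIV status elsewhere when it means to use it.

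**Conclusion.** The concern holds as a conditional efficiency point. The stated primary model ignores both stratification factors, at odds with most of the protocol's own secondary analyses. The consequence depends on whether HIV status predicts EFA: no loss if it does not, and roughly 2 to 8 power points for slope differences of 0.10 to 0.15, always in the conservative direction. These sizes rest on the assumed 20% to 35% uninfected share, a two-sided 5% test and a within-stratum slope SD of 0.139. Confidence is high on the omission and the direction, and low on the size.

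**What to change.** Before any arm-level results are seen, add HIV status and HIV status × time as fixed effects to the primary mixed model, and keep treatment × time as the primary contrast. The × time term matters: a main effect alone mainly adjusts the intercept, and EFA is a slope. Add hospital and hospital × time as well if the left-censored model converges with 50 patients, and state in advance which terms are dropped first if it does not.

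The Trial status section says enrolment has ended and analysis is under way in an open-label trial. If unblinded results have already been seen, leave the primary model as written and report the adjusted model as a labelled sensitivity analysis.

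Secondarily, rest any claim that the effect differs by HIV status or fungal burden on a treatment × time × subgroup interaction, and present subgroup estimates with confidence intervals as descriptive.

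The cost is a sentence or two of analysis wording and two to four model terms. HIV status and hospital are already recorded for randomisation. The simulation shows no material loss of power if HIV status turns out not to matter. Convergence of the censored model is the one practical risk and should be tested on data pooled without arm labels.
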